Earlier studies have focused primarily on the clinical relevance of the conventional troponin T (TnT) or I (TnI) in patients with critical illness but did not examine well the newer high-sensitive TnT (HsTnT) which has a higher sensitivity and shorter time to detect minor myocardial damage [9]. An earlier study reported a higher rate of mortality in patients with elevated serum troponin levels as compared to normal troponin in isolated TBI patients [17]. The high-sensitive troponin I was tested in patients with mild TBI, and authors [18] have reported a significant association between positive HsTnI and the abnormal head CT scan findings as compared to a negative CT scan in those with negative HsTnI. A recent meta-analysis [19] reported that among TBI patients, the effect of elevated troponin on mortality had a pooled odds ratio (OR) of 3.3, which is almost like that reported in non-traumatic brain injuries studies.

A recent study from our center revealed an all-cause mortality of 26% in TBI patients and the mortality rate was 4-fold higher in those who presented with elevated HsTnT levels [20]. In this study, positive HsTnT was reported in 65% of patients with moderate to severe TBI. Moreover, on multivariate regression analysis, positive HsTnT was an independent predictor of in-hospital mortality even after adjusting for any chest trauma [20]. Myocardial injury, defined as at least single cardiac troponin concentration above the 99th percentile upper reference limit, has been reported following TBI with a likely dose-response relationship with the severity of the head injury [21]. In patients with isolated TBI, a recent study found significant correlations between the on-admission TnI value and Glasgow Coma Scale (GCS), head Abbreviated Injury Scale (AIS), and Acute Physiology and Chronic Health Evaluation II score (APACHE II) [22].

Beta-adrenergic receptor blockers (BBs) may reduce the cascade of immune and inflammatory changes associated with injury as well as the heart rate and blood pressure. Blunting the beta-adrenergic sympathetic surge using BBs has been shown to reduce mortality post-trauma and post non-cardiac surgery in several studies [8, 16, 23–25]. Early administration of propranolol was found to be independently associated with lower mortality among patients with moderate to severe TBI (adjusted odds ratio, 0.25) and having a better functional outcome (GOS-E) at 6-month follow-up [25, 26].

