### Participants and study setting

The trial setting is the Hamad level I Trauma Centre in the state of Qatar, and the study subjects will be screened and enrolled from the trauma room in the emergency department (ED). Inclusion criteria are adult patients (≥ 18 to ≤ 65 years old) who sustained mild-to-severe blunt TBI (head AIS 1-5 and/or GCS 4-15), screened and enrolled within the first 24 h post-trauma.

Exclusion criteria are non-survivable injuries (head AIS = 6 and GCS = 3), uncontrolled bleeding on arrival to ED, SBP ≤ 100 mmHg (or MAP < 70 mmHg) not responding to initial resuscitation or required to be maintained on vasopressors for persistent hypotension (up to 24 h), patients with bradycardia [HR < 60] (re-assess every 2 h), pregnant women, prisoners, known to have severe bronchial asthma, and who requires emergency surgery < 6 h and no longer under trauma team care.

We expect to recruit a total of 771 TBI patients over 2 years. On hospital arrival, all TBI patients will have an initial head CT scan and managed according to the Advanced Trauma Life Support (ATLS) guidelines. We have a neurocritical care team with the state-of-art monitoring, imaging, and management of TBI. For this study, all mild-to-severe TBI patients who required hospital admission will be screened and enrolled by the attending physician and assigned nurse, if the subject meets the eligibility criteria. All enrolled patients will be tested for HsTnT (on admission and to be repeated after 6 h if the first reading is normal) and those who had positive HsTnT will receive BB, if no contraindication (group 1). Subjects with negative HsTnT (2 consecutive tests) will be randomized to either group 2, HsTnT –ve and BB use, or group 3, HsTnT –ve and no BB (placebo) (SPIRIT, Fig. 1).

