### Statistical analysis plan

The proposed sample size is based on an estimated rate of 12% reduction in mortality with the use of BBs in TBI patients reported by Salim et al. [13], having 80% power and 5% alpha error; the estimated sample size would be 257 subjects (including 5% dropout) in each study group (total 771 patients).

All analysis will be blinded to treatment assignment and will be performed by an independent biostatistician at Hamad Medical Corporation. We will also perform multivariate logistic regression analysis after adjusting for relevant covariates in addition to the differential intervention with an adjusted risk ratio and 95% confidence interval for the probability of death. Analysis will be based on intension-to-treat. Additional exploratory analyses will be performed for continuous variables such as marker of brain injury, injury severity scoring and head Abbreviated Injury Scale, cytokine level by comparing their distributions between intervention arms, and then by multiple linear regression models including other potential covariates of interest. We will explore the effectiveness of the intervention in subgroups using stratified analysis as well as multivariable models. The response to BBs use based on the type of brain lesion will be analyzed. Data analysis will be carried out using the Statistical Package for Social Sciences version 26 (SPSS Inc. USA).

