### Data and safety monitoring and interim analyses

An independent data safety monitoring board (DSMB) will monitor and assess the safety of the trial and review the serious adverse events across the study duration. The DSMB will comprise of experts in clinical trials, biostatistics and trauma care. The DSMB meetings will be held every 3 months. All adverse events will be reported to the institutional review board (IRB) and to the DSMB members. Unanticipated /fatal adverse events will be reported to the IRB within 24 h of the determination of unanticipated adverse event by the research team. The investigators will perform interim safety analyses at 12 and 24 months following 25% (*n* = 193) and 50% (*n* = 386) patient recruitment. The PI will keep IRB posted regarding DSMB review outcomes (PI will submit the minutes of the DSMB meeting report to IRB). All fatal events will be reported by the PI to the DSMB and IRB within 24 h of their incidence. If the mortality rate exceeds more than 50% in any therapeutic arm, the study team will stop the study and notify IRB.

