## Discussion

From the therapeutic point of view, BBs use was reported to have better survival in blunt TBI patients [4, 13, 14, 25, 26, 34–40]; however, double-blind RCTs remain lacking. Despite the optimistic results from prior data, a protocolized early BBs use is not currently a routine practice in patients sustaining TBI. Moreover, the release of cardiac troponin after head injury needs more scientific elaboration and physician awareness. A recent meta-analysis involving 12,721 patients showed that administration of BBs after TBI was associated with a significant reduction in adjusted in-hospital mortality (OR, 0.39) [35]. Retrospectively, Salim et al. [13] reported that patients with severe TBI who did not receive BBs had a mortality rate of 36% vs. 24% in those who received BBs (*p* = 0.036). Furthermore, if troponin-I was elevated on admission, the hospital mortality increased to 48.5% in patients without BBs therapy vs. 22.4% in those who received BBs (*p* = 0.026). In brief, the greatest survival benefit was observed retrospectively in the BBs group based on the conventional troponin positivity on admission.

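### The 257 per group and the 771 total agree only if one third of enrolled patients are HsTnT-positive; above that share the randomised arms fall short, and no prevalence is stated

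*Protocol article*

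**What the plan says.** The sample size paragraph (Statistical analysis plan) starts from a mortality difference: "The proposed sample size is based on an estimated rate of 12% reduction in mortality with the use of BBs in TBI patients", "having 80% power and 5% alpha error". It concludes that "the estimated sample size would be 257 subjects (including 5% dropout) in each study group (total 771 patients". The Discussion gives the rates behind the 12 points: in a retrospective severe-TBI series, patients without beta blockers "had a mortality rate of 36% vs. 24% in those who received BBs".

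Under Participants and study setting, overall recruitment is given as "We expect to recruit a total of 771 TBI patients over 2 years". All enrolled patients are tested for HsTnT, and "those who had positive HsTnT will receive BB, if no contraindication (group 1"). Patients negative on two tests are randomised to propranolol or placebo. The Randomization section applies the 1:1 ratio to the HsTnT-negative patients only, and the Discussion confirms that troponin-positive patients are not randomised.

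The one prevalence figure is in the Introduction, from an earlier study at the same centre: "positive HsTnT was reported in 65% of patients with moderate to severe TBI". The trial itself also admits mild TBI.

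**The concern.** Three equal groups of 257 would follow from a three-way allocation. This design has none: the share of patients who are HsTnT-positive decides how many enter group 1, and what is left is halved. The group sizes and the total are therefore linked through a prevalence that the article neither states nor supports.

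Group 2 versus group 3 is the only randomised comparison, so it is the only unconfounded test of whether propranolol lowers mortality. Group 1 differs from both by a strong prognostic marker; the Introduction reports four-fold higher mortality with raised HsTnT. Extra group 1 patients cannot stand in for missing randomised ones. If recruitment ends at 771 overall and more than a third are positive, the randomised comparison ends below its stated size and below 80% power.

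**Working it through.** **Inputs.** From the article: 36% vs 24% mortality (Discussion); 80% power, 5% alpha, 5% dropout, 257 per group and 771 in total (Statistical analysis plan); 1:1 allocation among HsTnT-negative patients (Randomization); 65% positive in moderate-to-severe TBI (Introduction). Assumed: a two-sided test, every HsTnT-negative enrolled patient is randomised, and all prevalences other than 65%.

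**Step 1: reproduce 257.** Pooled two-proportion formula with mean rate 0.30 and difference 0.12:

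n = [1.960 × √(2 × 0.30 × 0.70) + 0.842 × √(0.36 × 0.64 + 0.24 × 0.76)]² / 0.12² = 227.7.

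Continuity correction: n_c = (n/4) × [1 + √(1 + 4/(n × 0.12))]² = 244.1. Dropout: 244.1/0.95 = 257.0. So 257 is a sound two-arm figure. Without the correction the same inputs give 228, then 228/0.95 = 240, which does not match. The total is 3 × 257 = 771.

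**Step 2: the prevalence that the total implies.** With a share p positive, each randomised arm has 771 × (1 − p)/2 patients. Setting this to 257 gives 1 − p = 514/771, so p = 1/3.

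**Step 3: arm size and power at other prevalences.** Patients per arm after dropout: e = 0.95 × 771 × (1 − p)/2. To match Step 1, the correction is applied as e_c = e × [1 − 1/(0.12 × e)]². Power is then Φ{[0.12 − 1.960 × √(0.42/e_c)] / √(0.4128/e_c)}, where 0.42 = 2 × 0.30 × 0.70 and 0.4128 = 0.36 × 0.64 + 0.24 × 0.76.

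Worked example at 65%: 771 × 0.35/2 = 135; e = 128.2; e_c = 112.1; power = 50%.

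| HsTnT-positive | Per randomised arm | After 5% dropout | Power, corrected | Power, uncorrected | Enrolments for 514 randomised, no cap |
|---|---|---|---|---|---|
| 20% (assumed) | 308 | 293 | 87% | 89% | 643 |
| 33.3% (implied) | 257 | 244 | 80% | 83% | 771 |
| 40% (assumed) | 231 | 220 | 75% | 79% | 857 |
| 50% (assumed) | 193 | 183 | 67% | 71% | 1,028 |
| 65% (Introduction) | 135 | 128 | 50% | 55–56% | 1,469 |

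The last column is 514/(1 − p). On the corrected basis there is no slack: 80% holds at one third positive and is lost above it.

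**Step 4: is one third plausible?** Suppose positivity is 65% in moderate-to-severe patients and m in mild ones. The share of moderate-to-severe patients that gives one third overall is (1/3 − m)/(0.65 − m): 47% for m = 5%, 42% for m = 10%, 30% for m = 20%. The values of m are assumptions. The article states no expected severity mix, so one third can be neither confirmed nor ruled out.

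**The case against.** A reader might infer that recruitment is fixed at 771 and that the trial is heading for 135 per arm and about 50% power. The article does not support that.

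- The 771 is an expectation, and the sample size paragraph states its requirement per group with the total in brackets. It can be read as recruiting until each group holds 257. This stands as far as it goes: the text is ambiguous. But the article states no point at which a group closes, enrols patients before HsTnT status is settled, and sets its interim looks at 193 and 386, which are 25% and 50% of 771. Either reading needs a sentence to make it hold.
- The 65% comes from moderate-to-severe TBI. The trial also takes mild TBI and excludes patients with uncontrolled bleeding or unresponsive hypotension, so its positivity is probably lower. This stands. Below one third the randomised arms would exceed 257.
- A condensed article may leave recruitment rules to the full protocol. That is why the missing cap is not the finding by itself. The finding is that the published group sizes and total do not follow from the published allocation without a prevalence that nothing in the article supports.

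A reader might also want the interim looks moved to the randomised count. They are described as safety analyses, and group 1 is on propranolol. At 65% positive, a look at 25% of 514 (about 129 randomised) would come at about 129/0.35, or 367–369 enrolled, instead of 193. That would delay safety review, so the looks should stay as they are.

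**Conclusion.** The point holds in conditional form. The 257 is correct for a two-arm comparison of 36% vs 24%; multiplying it by three is not justified when one group is filled by a biomarker result. The stated sizes are consistent only at one third HsTnT-positive. Above that, ending at 771 takes the randomised comparison below its stated 80% power: to about 75% at 40% positive, 67% at 50% and, as an upper-range scenario, 50% at 65%. Below one third there is no loss.

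These figures accept the article's mortality rates and assume a two-sided, continuity-corrected calculation with 5% dropout. The actual prevalence, and therefore the direction and size of any deviation, is unknown. It should be fixed; the article does not show that a shortfall will occur.

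**What to change.** In Participants and study setting and in the Statistical analysis plan, define the recruitment target as 514 randomised HsTnT-negative patients (257 + 257), and stop enrolling into group 1 once it holds 257. Total enrolment then does not exceed 771, and is lower if fewer than one third are positive.

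The cost is protocol wording and a running count by group, more screening, possibly longer accrual, and a group 1 that is no longer consecutive after the cap. At 65% positive about 1,469 patients would have to be tested to find 514 negatives. Once group 1 is full, enrolment would have to wait for the HsTnT result. The cap also limits the HsTnT-positive sample for the exploratory biomarker correlations. The 257 for group 1 is kept only to preserve the total, since the two-arm formula does not size that group.

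If 771 is kept without a cap, state the HsTnT positivity assumed for the mild-to-severe population, and restate the randomised arm size and power over a plausible range, as in the table above. Leave the interim safety looks on total enrolment under either option.

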### Data and safety monitoring and interim analyses

An independent data safety monitoring board (DSMB) will monitor and assess the safety of the trial and review the serious adverse events across the study duration. The DSMB will comprise of experts in clinical trials, biostatistics and trauma care. The DSMB meetings will be held every 3 months. All adverse events will be reported to the institutional review board (IRB) and to the DSMB members. Unanticipated /fatal adverse events will be reported to the IRB within 24 h of the determination of unanticipated adverse event by the research team. The investigators will perform interim safety analyses at 12 and 24 months following 25% (*n* = 193) and 50% (*n* = 386) patient recruitment. The PI will keep IRB posted regarding DSMB review outcomes (PI will submit the minutes of the DSMB meeting report to IRB). All fatal events will be reported by the PI to the DSMB and IRB within 24 h of their incidence. If the mortality rate exceeds more than 50% in any therapeutic arm, the study team will stop the study and notify IRB.

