### Study end points and completion

We expect to complete the targeted subject recruitment and follow-up within 24 months. A subject will be in the research study until 3 months post enrolment or death. Patients will be followed up for Functional Independence Measure (FIM) at the latest time measured and Glasgow Outcome Score (GOS) at 3 months (in the clinic or through telephonic script). Patients and/or their next-of-kin will be asked to provide contact numbers to assess the outcome during follow-up.

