## Trial status

The study started recruitment on 29 December 2020 and to be completed in 31 December 2022. The study was registered on 07 August 2020 at ClinicalTrials.gov (identifier number: NCT04508244).

Date and version identifier:

Protocol code: BBTBBT

Version: August 20; 2020

MRC, Hamad Medical Corporation: IRGC-05-SI-18-293

Amendment: 29 July 2020 and 23 February 2021 (the initial time widow to administrate BB was the first 12 h; it has been amended to be the first 24 h; this will ensure better hemodynamic stability before starting BB).

IRB-A-HMC-2019-0014

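### The 50% recruitment look is dated to the planned end of the trial, and the only stated stopping criterion compares no arms and is insensitive at the mortality expected in the randomised patients

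*Protocol article*

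**What the plan says.** Under Data and safety monitoring and interim analyses, the protocol article states: "The investigators will perform interim safety analyses at 12 and 24 months following 25" per cent (193 patients) and 50% (386 patients) of recruitment. The same section gives one explicit criterion for ending the trial: "If the mortality rate exceeds more than 50% in any therapeutic arm, the study team will stop the study and notify IRB". It also provides an independent DSMB with biostatistical expertise that meets every 3 months and reviews serious adverse events. Every death is to reach the DSMB and the IRB within 24 hours.

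Three other sections fix the trial's length:
- Participants and study setting: "We expect to recruit a total of 771 TBI patients over 2 years".
- Study end points and completion: "We expect to complete the targeted subject recruitment and follow-up within 24 months", and for each patient, "A subject will be in the research study until 3 months post enrolment or death".
- Trial status: "The study started recruitment on 29 December 2020 and to be completed in 31 December 2022".

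On who analyses, the Statistical analysis plan section says "All analysis will be blinded to treatment assignment" and assigns the work to an independent biostatistician. The monitoring section has the investigators perform the interim analyses and the study team stop the trial.

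Only troponin-negative patients are randomised, 1:1 to propranolol (Group 2) or placebo (Group 3). Eligible troponin-positive patients all receive propranolol (Group 1).

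**The concern.** Half of recruitment cannot fall at month 24 if recruitment and follow-up are complete by month 24. If the calendar date is followed, the second look comes when no patient remains to be protected by it.

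The stopping criterion looks at the absolute death rate in one arm. Harm from propranolol in the randomised patients means more deaths in Group 2 than in Group 3. Where background mortality is low, a large relative increase still leaves Group 2 far below one half. Group 1 has the worst prognosis and no control, so crossing the threshold there need not say anything about the drug. At stake is whether the written criterion would act on a real excess of deaths in Group 2, and whether it might stop the trial on prognosis in Group 1.

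**Working it through.** **1. Interim counts and calendar.** The counts reproduce: 0.25 × 771 = 192.75 (193) and 0.50 × 771 = 385.5 (386). The dates do not fit them.
- Even accrual over 24 months: 771/24 = 32.1 per month, so 193/32.1 = 6.0 months and 386/32.1 = 12.0 months.
- If the last patient must also complete 3 months of follow-up by month 24, accrual has 21 months: 771/21 = 36.7 per month, giving about months 5.3 and 10.5.
- If 386 really falls at month 24, full recruitment takes 24 × 771/386 = about 48 months.
- If the sentence means 12 and 24 months after those counts are reached, both looks come later still.

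**2. Expected mortality by troponin status.** The Introduction gives, from the centre's own study, 26% mortality overall, a 4-fold higher rate if troponin is elevated, and 65% positive in moderate to severe injury. Assume that these describe one cohort. With m the mortality in negatives, 0.26 = m × (0.65 × 4 + 0.35), so m = 0.26/2.95 = 8.8%, and 4m = 35.3% in positives. The trial also enrols mild injury, so the positive share is uncertain:
- 80% positive: 0.26/(0.8 × 4 + 0.2) = 7.6% in negatives.
- 30% positive: 0.26/(0.3 × 4 + 0.7) = 13.7% in negatives.

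**3. Chance that the rule fires in Group 2.** Three groups of 257 are planned. Assuming equal thirds, the looks have 193/3 = about 64 and 386/3 = about 128 per arm. The rule fires if deaths exceed n/2. With deaths binomial(n, p):

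| True Group 2 mortality | 64 per arm | 128 per arm |
|---|---|---|
| 17.6% (8.8% doubled) | 7 × 10⁻¹⁰ | 1 × 10⁻¹⁷ |
| 26.4% (8.8% tripled) | 1.6 × 10⁻⁵ | 4 × 10⁻⁹ |
| 41% (13.7% tripled) | 5.8% | 1.6% |
| 48% (36% plus 12 points) | 33% | 29% |

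The last row starts from 36%, the untreated mortality in the retrospective severe-injury cohort behind the sample size (36% against 24%, Discussion).

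**4. What a between-arm comparison would show.** As a benchmark, take z = (p₂ − p₃)/√(2p̄(1 − p̄)/n), with p̄ the pooled proportion, and call z > 2 a signal. Simulation of cumulative looks at 64 and 128 per arm, with 8.8% in Group 3, gives the chance of a signal at either look:
- no effect: about 3.7%
- mortality doubled: about 58%
- mortality tripled: about 97%

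**5. Group 1.** At a look of 64, the chance of exceeding 50% depends on the true rate:
- 48.5%, the untreated troponin-positive rate in the Discussion: about 36%
- 35.3%, from step 2: about 0.5%
- 22.4%, the treated rate in the same comparison: about 3 × 10⁻⁷

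**The case against.** The strongest reply is that the 50% rule is not the safety system. An independent DSMB meets every 3 months (about eight times in 24 months), reviews serious adverse events and hears of each death within 24 hours. None of this depends on the rule or on the two dates. A DSMB charter, not shown, may hold comparative boundaries. This stands: a reader might infer that safety monitoring does not work or that the second look leaves patients unprotected, and the document does not support either.

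A reader might also infer that the rule cannot detect harm at all. That is too strong. From a 36% control rate, a 12-point harm would trigger it at a look about one time in three.

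For Group 1, a reader might expect frequent false stops. If running mortality were watched from the first patient, a true 35.3% would cross 50% at some point in about 54% of trials. But no section says the rule is applied patient by patient, and much of that figure is simply the first patient dying. On the same basis Group 2 would cross in about 21% (doubling) and 36% (tripling). Compared fairly, at the looks, Group 1 at 35% hardly ever crosses. Since Group 1 is treated, the 22.4% rate deserves as much weight as the 48.5%.

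Last, a reader might infer that blinded staff will see unblinded mortality. The article does not say so. A per-arm threshold can be checked on coded arms, and Group 1 is not randomised. What remains is loose wording about who analyses and who decides.

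None of this resolves the calendar conflict, which lies within the article, or makes the stated criterion comparative.

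**Conclusion.** Two points hold. First, the interim timing contradicts the 24-month plan: at even accrual the two counts fall at about months 6 and 12, not 12 and 24, and the 50% look as dated coincides with the planned end. This rests only on the article's own dates and counts.

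Second, the one explicit stopping criterion compares no arms, sets no minimum number, and has practically no chance of firing at a look if propranolol doubles or triples a mortality of 8.8%, where a simple between-arm comparison would usually show a tripling and more often than not a doubling. This rests on reading the 26%, 4-fold and 65% figures as one cohort and on equal group sizes. The insensitivity weakens as mortality rises: about 6% at the first look for a tripling of 13.7%, and about one in three for a 12-point harm from 36%. In Group 1 a trigger could reflect prognosis, with a likelihood anywhere from near 0 to about 36% at a look of 64, depending on which of the article's rates applies.

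The DSMB and the reporting of deaths are separate safeguards. The finding concerns the written criterion and schedule, not monitoring as a whole.

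**What to change.** - **Timing.** Reconcile the interim schedule with the 24-month plan, for example by triggering the looks on recruitment counts instead of calendar months.
- **Harm criterion.** Add a between-arm guideline on Group 2 versus Group 3 mortality, with a boundary that the DSMB sets in advance. State that the 50% rule is not the only ground for action. If a DSMB charter already contains such a guideline, refer to it.
- **Group 1.** Have the DSMB review it separately, with a minimum number of patients before any mortality threshold is applied.
- **Roles.** Reconcile the monitoring section with the Statistical analysis plan section: the independent biostatistician reports arm-level mortality to the DSMB, and the DSMB makes the recommendation.

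The cost is wording in the protocol and the DSMB charter, plus the DSMB's time to agree a boundary. The looks use mortality data that the trial already collects, and no added patients are needed.
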